### Smartphone triage tool

St George's Vascular Institute and the London Ambulance Service have developed a scoring system to diagnose rAAA based on ten key parameters. The score was developed with logistic regression of ambulance records and Hospital Episode Statistics (HES) data for 2200 patients from 2005 to 2010. The score used routine ambulance clinician assessments and detected rAAA with 82.6% sensitivity (area under the receiver operating characteristic (ROC) curve 0.86). The parameters collected by the app are: age, gender, blood pressure, capillary refill time, temperature, and history of collapse, back pain, diabetes, cancer or peripheral vascular disease. This triage tool has been integrated into a secure mobile app available for smartphones on all major operating systems. This mobile app has been made available to all LAS clinicians for the observational study since November 2014. LAS clinicians, including paramedics, paramedic students and technicians, will download the app onto their own personal smartphone. A website was set up to coordinate educational meetings and provide regular study updates.^18^ LAS clinicians are advised to enter physiological parameter data as soon as it is safe to do so from a clinical perspective using the first available set of observations, and in the same circumstances as completing existing patient report forms (PRFs). Pilot results show that data entry takes an average (mean) of 16 s per patient. There will be no change to the underlying logistic regression model during the course of the study, and no intention to update or modify the app thereby preventing issues with version control. The app design prevents the saving of incomplete data entry at the point of care. Incomplete patient records will be included in the analysis, where possible as per the Strengthening the Reporting of Observational Studies in Epidemiology (STROBE) guidelines. There is the possibility for incomplete data in terms of diagnosis retrieval, outcome (mortality) retrieval and discordance between the PRF data and the app data. Owing to the study design, we will not be able to follow-up eligible patients whose data are not originally included in the app. This should not prove a limitation of the study as the aim of the study is to assess the sensitivity and specificity of the model for prediction of rAAA. Assessment of any incomplete data entries will provide an outcome measure regarding potential app user error rate. This will include a sensitivity analysis whereby the ROC curve for mortality and rAAA diagnosis using each combination of ‘app data’, ‘PRF data’ and ‘app/PRF concordant data’ will be produced.

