### Statistical analysis

True positive and true negative diagnoses will be defined according to the hospital discharge record retrieved by site investigators at each participating hospital. Contingency table analysis will allow reporting of sensitivity, specificity, positive predictive and negative predictive rates for the logistic score, with CIs determined by sample size. The development and validation data sets will be further explored for model refinement using a logistic regression approach, with the same entry variables entered into forward selection, removal from models at p<0.1, and significance ascribed at p<0.05. An ROC curve will be reported for rAAA diagnosis using the original logistic score, and the refined score at the study end. Separate logistic models will be designed to explore 30-day mortality. Where diagnosis or mortality data cannot be retrieved, ROC analysis is impossible. As per STROBE guidelines, this study will fully describe the available data for patients with diagnoses/mortality and those without diagnosis/mortality, and subject the demographics/presenting features of both cohorts to statistical comparison to explore whether the absence of diagnosis data has introduced selection bias to the study.

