### Patient pathway

The patient pathway and data collection is outlined in figure 1. The data collection process uses a pre-existing service evaluation framework currently in use by LAS to identify in-hospital discharge diagnosis for patients using their service. At no point does this study alter patient triage, treatment or destination. A secure website was set up to collect and store the logistic score from the app.

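### The plan calls ROC analysis impossible where no diagnosis is retrieved, so it can detect selective retrieval but not correct it, although every saved patient has a score

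*Protocol article*

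**What the plan says.** The Primary outcome section of the protocol article makes sensitivity and specificity the primary outcome. Under Statistical analysis the reference standard is fixed: "True positive and true negative diagnoses will be defined according to the hospital discharge record retrieved by site investigators at each participating hospital". Missing diagnoses are expected, since the Smartphone triage tool section says "There is the possibility for incomplete data in terms of diagnosis retrieval, outcome (mortality) retrieval and discordance between the PRF data and the app data". No expected rate is given.

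The response to missing diagnoses is in Statistical analysis. It opens with "Where diagnosis or mortality data cannot be retrieved, ROC analysis is impossible". It then plans to describe patients with and without these data and to test their demographics and presenting features against each other, "to explore whether the absence of diagnosis data has introduced selection bias to the study". It names no correction, imputation or bounding analysis.

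Two other statements bear on what is possible. The Smartphone triage tool section says "The app design prevents the saving of incomplete data entry at the point of care", and Patient pathway says "A secure website was set up to collect and store the logistic score from the app".

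**The concern.** Taken together, these statements mean that a saved patient always has the ten predictors and the score, and that only the reference diagnosis can be missing. Methods for an index test known in everyone and a reference standard known in some were made for this situation. The plan instead closes the question by calling the analysis impossible.

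Under the stated definition, a patient without a retrieved discharge record is neither a true nor a false result and cannot enter the contingency table. So the primary estimates, and not only the ROC curve, would in effect be complete-case. If retrieval varies with the score, or with predictors such as age, blood pressure or collapse, those estimates are shifted. The planned cohort comparison might flag this but would not say how far sensitivity and specificity have moved, and a non-significant result would not show that they have not.

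**Working it through.** **Inputs from the article (Power calculation).** 150 rAAA, 1000 controls, expected sensitivity 83% (75.9% to 88.2%), expected specificity 73% (69.0% to 78.3%).

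**The plan's own intervals.** 124/150 gives 75.8% to 87.9% (Wilson) or 75.6% to 88.4% (Clopper-Pearson), close to the stated sensitivity interval. 730/1000 gives 70.2% to 75.7% (Wilson), narrower than the stated 69.0% to 78.3%. That mismatch is a separate matter and does not affect this point.

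**Expected table with full retrieval.** True positives 0.83 × 150 = 124.5; false negatives 25.5; false positives 0.27 × 1000 = 270; true negatives 730. Score-positive total 394.5; score-negative total 755.5.

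**Complete-case estimates.** Let a be the share of score-positive and b the share of score-negative patients whose diagnosis is retrieved. Both are assumptions.

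- Sensitivity = 0.83a / (0.83a + 0.17b)
- Specificity = 0.73b / (0.73b + 0.27a)

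For a = 0.95 and b = 0.80: 0.7885 / (0.7885 + 0.136) = 85.3%, and 0.584 / (0.584 + 0.2565) = 69.5%.

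| Retrieval, score-positive / score-negative | Sensitivity | Specificity |
|---|---|---|
| 80% / 80% | 83.0% | 73.0% |
| 95% / 90% | 83.7% | 71.9% |
| 95% / 80% | 85.3% | 69.5% |
| 95% / 70% | 86.9% | 66.6% |
| 80% / 95% | 80.4% | 76.3% |

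**Correction with the known scores (Begg-Greenes).** Predictive values from verified patients are applied to all score-positive and score-negative patients. At 95%/80%: PPV = 118.275 / 374.775 = 31.6%, and 0.3156 × 394.5 = 124.5 true positives; NPV = 584 / 604.4 = 96.6%, leaving 25.5 false negatives among 755.5. Sensitivity is again 83.0% and specificity 73.0%. The same holds in every row, because retrieval there depends only on the score.

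**Where the correction fails.** Suppose a fraction f of all rAAA patients die without a retrieved diagnosis and all of them were score-positive (an extreme assumption). Complete-case sensitivity is (0.83 − f) / (1 − f).

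- f = 0.10: complete-case 81.1%. PPV = 109.5 / 379.5; times 394.5 = 113.8; corrected 113.8 / (113.8 + 25.5) = 81.7%.
- f = 0.20: complete-case 78.8%. PPV = 94.5 / 364.5; times 394.5 = 102.3; corrected 102.3 / (102.3 + 25.5) = 80.0%.

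Against a true 83%, only about 30% of the bias is removed. If retrieval depends on disease alone (95% of cases, 80% of controls), complete-case stays at 83.0%/73.0% while Begg-Greenes moves to 82.3%/74.0%.

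**Bounds.** At 95%/80% retrieval, 0.05 × 394.5 = 19.7 score-positive and 0.20 × 755.5 = 151.1 score-negative patients are unverified.

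- Best case (unverified positives all rAAA, unverified negatives all controls): sensitivity (118.3 + 19.7) / (138.0 + 20.4) = 87.1%; specificity (584 + 151.1) / (735.1 + 256.5) = 74.1%.
- Worst case (the reverse): sensitivity 118.3 / (118.3 + 20.4 + 151.1) = 40.8%; specificity 584 / (584 + 256.5 + 19.7) = 67.9%.

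**The case against.** The strongest reply is that nothing in the article suggests that the score drives retrieval. Patient pathway describes a pre-existing ambulance service framework for finding discharge diagnoses, and the study does not alter care. If retrieval is unrelated to the score there is no bias, and if it depends only on disease the complete-case estimates are the sound ones and a score-based correction makes them slightly worse. The retrieval rates above are assumed. The authors foresaw the problem, named selection bias and committed to comparing the two groups; the choice of imputation or weighting is often left to an analysis plan, which is not shown here.

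Most of this stands. It limits the point to a risk of unknown size and direction. It does not rescue the sentence, which is not silence left for a later document but a stated rule, wrong as a general claim, that rules out the remedies.

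Three stronger readings are tempting and are not supported:

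- **That bias does enter.** The article gives no retrieval rate and no link between retrieval and score.
- **That the article contradicts itself**, because the Smartphone triage tool section says "Incomplete patient records will be included in the analysis, where possible". A rule qualified in that way and a named case where it is held not to be possible are consistent.
- **That rAAA patients who die early have no diagnosis and could be classified from the cause of death or emergency department record.** The article does not say that such patients lack a discharge diagnosis. Some may have a record naming another condition and would then be misclassified, not dropped. It mentions retrieval of mortality, but not of cause of death or emergency department records.

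**Conclusion.** The point holds as a risk that the plan leaves uncorrected. As written, the plan implies unadjusted complete-case estimates of sensitivity, specificity and AUC; exclusion from the contingency table is inferred from the reference-standard definition and is not stated outright. The claim of impossibility is wrong, because score and predictors are known for every saved patient.

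For size, at 95%/80% retrieval the shift is +2.3 points in sensitivity and −3.5 in specificity; at 80%/95% it is −2.6 and +3.3. The sensitivity shift is well inside the plan's own interval, whose half-width is (88.2 − 75.9) / 2 = 6.2 points. The 3.5-point specificity shift exceeds the half-width of about 2.8 points calculated for 1000 controls, though not that of the wider interval the plan prints (about 4.7). All of this rests on assumed retrieval rates and on true values of 83% and 73%.

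**What to change.** Replace the sentence on impossibility with wording such as: complete-case estimates are the main analysis; in a prespecified sensitivity analysis, sensitivity, specificity and AUC are re-estimated using the known scores of patients without a retrieved diagnosis, by Begg-Greenes correction, inverse-probability weighting or multiple imputation of diagnosis, assuming that diagnosis is missing at random given the score and app variables; best-case and worst-case bounds for unretrieved diagnoses are reported alongside. Keep the planned comparison of patients with and without a diagnosis as description.

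The bounds are needed because loss that depends on the diagnosis itself, for instance through early death, is not removed by the correction. Complete-case results should stay visible because they are the better estimate if retrieval depends only on disease.

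The cost is a change of wording and modest extra analysis of data already collected, with no effect on recruitment or care. The downside is that the bounds may be wide: in the worked example those for sensitivity run from 40.8% to 87.1%, because each control far outnumbers each case among unverified score-negative patients and the worst case counts all of them as rAAA.

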### Patient pathway

The patient pathway and data collection is outlined in figure 1. The data collection process uses a pre-existing service evaluation framework currently in use by LAS to identify in-hospital discharge diagnosis for patients using their service. At no point does this study alter patient triage, treatment or destination. A secure website was set up to collect and store the logistic score from the app.

**Figure 1 BMJOPEN2016011308F1:**
[figure not shown]
Flow diagram indicating patient and data pathway for FILTR prospective multicentre observational study. CAD, computer-aided dispatch log; DOB, date of birth; LAS, London Ambulance Service.

### Informed consent

LAS clinicians, in line with General Medical Council (GMC) guidance regarding consent in emergencies, will not need to seek formal consent from patients in order to enrol them in this observational study. This is determined on the basis that patients with suspected rAAA may be in extremis and therefore treatment provided is immediately necessary to ‘save their life to prevent serious deterioration of their condition’ (GMC Guidance on Consent). This has been discussed with the NHS Health Research Authority, who agree that this is appropriate given the nature of the study. No patient-identifiable data are collected during the course of medical assessment and transfer to definitive care.

### Treatment and follow-up

This observational study will have no impact on triage, treatment or follow-up for the patients involved.

## Discussion

In-hospital mortality for rAAA who survive to the point of hospital admission is estimated to be 65.9% for England,^19^ with lower mortality achieved in the group selected for operative management, where 1-year mortality is 38.6% following EVAR and 42.8% following open repair.^3^ There remains ongoing uncertainty regarding how to reduce mortality with many non-operative factors being key determinants of survival. Current recommendations suggest that reductions in mortality might be achieved by rapid direct transfer to a high-volume specialist centre, that offers ready availability of the full spectrum of endovascular and open surgical care, with appropriate support facility and intensive care. This is at odds with existing prehospital service provision for patients with suspected rAAA, who are usually taken to the nearest hospital, often requiring secondary interhospital transfer for definitive care. Prehospital triage systems have been shown to be successful for other conditions such as major trauma, STEMI and stroke, and there are possibly significant implications if a similar system could be implemented for rAAA.^15–17^ Challenges for such an approach will include the diagnostic accuracy with which rAAA can be triaged at the scene of the emergency, and also the fate of patients incorrectly diagnosed with rAAA and nonetheless subjected to prolonged transfer and management at a vascular centre. Finally, outcomes in patients with rAAA that were not identified will also require investigation and estimation.

Given this study links prehospital and hospital care, an extensive collaborative approach has been employed to the benefit of the study design and patient pathway. In order to be pragmatic, existing information pathways for data collection have been used and the smartphone app records only routinely collected data. At no point does this study alter patient triage, treatment or destination, but it may provide support for an efficacy study of field triage in the future.

This prospective validation study uses an observational approach to test the diagnostic accuracy of a smartphone triage tool to support clinical decision-making for the diagnosis of rAAA at the scene of the emergency. We anticipate that assessment and validation of the smartphone triage tool will provide feasibility evidence for the use of smartphones in the emergency setting and their use in a prospective observational study; as well as provide data for whether such an approach could be beneficial to patients with rAAA without unacceptable consequences for the wider population with differential diagnoses suspected to be rAAA. The study is potentially limited by geographical issues, such as generalisability beyond London to less urban healthcare settings. It will not be possible to collect data for patients eligible but not recruited in FILTR, and the reliability with which paramedics use each aspect of the app will not be monitored prospectively, though retrospective audit will be performed between LAS paper records and electronic FILTR records for each included patient. It is not possible to identify which data fields are most difficult to enter due to the app not saving incomplete data entry sets.

### Status

The study started recruitment in November 2014 and will close recruitment in November 2016.
